#### 1.2.4. Quantitative Part of the Study

General objective: To understand how the youth population of Catalonia evaluates the WSJ.

Specific objectives:To determine what content of the WSJ receives the best rating by young people.To identify whether assessment of content and usability of the WSJ varies according to the following factors: age, sex, gender identity, sexual orientation, culture of origin, socioeconomic status, area of residence (urban, semiurban or rural) and motivation for consulting the website (of their own accord or suggested by a professional).To identify whether assessment of content of the WSJ is different in young people that had previously used it.To assess if having previously consulted the ASSIR unit is associated with a different assessment of the WSJ content.To determine if the target population knows about the WSJ, and what percentage use it and consider it useful.To evaluate if socioeconomic conditions determine the use of paper vs. digital questionnaires.To determine if young people in Catalonia visit other affective-sex education websites, and which are the most popular.To determine if young people in Catalonia follow any influencers for affective-sexual education, and which influencers are the most popular.To determine the percentage of young people in Catalonia that visit pornography websites.

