#### 2.4.2. Quantitative Part of the Study

In the context of COVID-19, we have both an online (Microsoft Forms) and paper version of the questionnaire (Teleform). The online questionnaire can be accessed via direct link or QR code. The questionnaire consists of 24 closed questions and 2 open-ended questions. The questionaire is available in Supplementary Material (Figure S1).

At the education centres: The recruiting researchers will communicate with these centres to disseminate the questionnaire among students. The centre directors will decide if their centre will use the online or paper questionnaire.At the ASSIR units: a wide network of professionals are also researchers that will recruit for the study. The study will be disseminated through posters in the waiting rooms and at the counter of each ASSIR unit. These posters will contain the study instructions and the QR code for the questionnaire so that young people can quickly download it to their mobile phone and answer it. There will also be a paper version of the questionnaire for people unable to access it digitally. Digital users of the ASSIR will be sent the link to the questionnaire with information to encourage them to answer on the same platform they used for the consultation (email, WhatsApp^®^, e-consultation).WSJ users who make email inquiries will automatically receive an email with the direct link to the questionnaire, encouraging them to participate after explaining that this is a study to evaluate the website. The study will be also advertised on the WSJ homepage through images with a direct link to the questionnaire.

Whatever the origin of the participant, the variables that will be evaluated for all the participants in the sample through the questionaire are the following:

Sociodemographic variables: age, sex, gender identity, sexual orientation, country/culture of origin, years of residence in Spain, postal code, socioeconomic condition of the postal code according to the Territorial Socio-Economic Index, city/rural/semirural residence, current job, ongoing studies, type of access to the questionnaire (electronic or paper).

Variables related to the WSJ: prior knowledge of the WSJ, use of the WSJ, usability of the WSJ, usefulness of the WSJ, rating of affective-sexual education content.

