Variables related to social media: ability to access to digital resources, use of other webpages of affective-sexual education, following affective-sexual education influencers, use of pornography webpages.

Variables related to study recruitment: Participants from educational centers and ASSIR units will access the survey by indication of the professionals. The third contacting group will access it by themselves, without anyone’s indication. The sample calculation has been performed based on this variable.

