Due to COVID-19, Microsoft Forms and Microsoft Teams software might be used. In this case, we will guarantee data protection, in accordance with the Regulation (EU) 2016/679 of the European Parliament and Council of April 27 on Data Protection (RGPD) and the Spanish Organic Law 3/2018 of December 5, on the Protection of Personal Data and guarantee of digital rights. The online questionnaire can only be answered by people aged 16 and over since the necessary consent cannot be obtained from children under 16. Consequently, the first question in the online questionnaire is if they agree to answer it, and the second if they are 16 or older. Responses from those under 16 will be collected using the paper questionnaire at the education centres and ASSIR units.

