#### 2.6.2. Quantitative Part of the Study

We will perform a descriptive analysis of all variables, using frequencies and percentages for categorical variables and mean and standard deviation for age and years living in Spain. Familiarity with the website will be summarized with a percentage and confidence interval. The bivariant analysis will be performed using Pearson’s chi-squared test or Fisher’s exact test to find associations between the assessment of WSJ and the sociodemographic variables. If the bivariant analysis shows any associations, a multivariant analysis using a regression model with assessment of WSJ as the outcome variable is planned. The anlaysis will be performed disaggregating by gender. Significance level is set at 5%. SPSS statistical package for Windows, version 25.0, will be used for all analyses.

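### The regression is fitted only if bivariate tests find an association, so adjustment of the age-unbalanced own-accord versus professional-indication contrast is left partly to chance

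*Protocol article*

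**What the plan says.** Section 2.6.2 plans Pearson chi-squared or Fisher tests "to find associations between the assessment of WSJ and the sociodemographic variables". It then says: "If the bivariant analysis shows any associations, a multivariant analysis using a regression model with assessment of WSJ as the outcome variable is planned". The significance level is 5%.

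The sample size in section 2.3.2 rests on comparing participants who came of their own accord with those who did not: 388 per group, 0.5 versus 0.4. Section 2.4.2 defines the groups by recruitment route. Education centres and ASSIR units form the indicated group. For the other group it says "The third contacting group will access it by themselves", and it adds "The sample calculation has been performed based on this variable". Section 1.2.4 lists this factor, and age, among those that may change the assessment of the website.

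Own-accord participants reach the questionnaire by an automatic email link or from the site itself: "The study will be also advertised on the WSJ homepage through images with a direct link to the questionnaire". Section 2.5 closes the online form to under-16s and continues: "Responses from those under 16 will be collected using the paper questionnaire at the education centres and ASSIR units". The study enrols ages 14 to 25 (section 2.3).

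**The concern.** Two stated features combine badly.

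First, a non-significant crude association is not a sound reason to leave a non-randomised comparison unadjusted. Confounders can mask one another, and a covariate whose own test misses 5% can still bias the contrast of interest.

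Second, age is unbalanced in the sized contrast because of how the questionnaire is delivered, whatever the recruitment luck. The indicated group can include 14–15-year-olds and the own-accord group cannot. If younger adolescents rate the website differently, part of any crude difference between routes is a difference in age.

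The tests that trigger the model are also described as covering the sociodemographic variables. Section 2.4.2 lists recruitment route under a separate heading, so the contrast that sized the study is not named among them.

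At stake is whether the headline comparison is reported crude or adjusted, a choice the plan hands to the data.

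**Working it through.** **1. The plan's own figure.** With 0.5 versus 0.4, two-sided alpha 0.05, power 0.80 and pooled variance:

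n = [1.96·√(2·0.45·0.55) + 0.842·√(0.5·0.5 + 0.4·0.6)]² / 0.10² = 387.3, so 388 per group and 776 in total.

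This matches section 2.3.2 exactly; power at 388 per group is 0.801. The calculation is that of a crude two-proportion comparison.

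**2. Where under-16s can appear.**

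| Route | Questionnaire | Ages possible | Group |
|---|---|---|---|
| Education centres | online or paper, as the director decides | 14–25 on paper, 16–25 online | indicated |
| ASSIR units | online, or paper | 14–25 on paper, 16–25 online | indicated |
| Website users | online link | 16–25 | own accord |

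**3. Size of the bias.** Let f be the share of under-16s in the indicated group and d the gap in favourable rating between under-16s and the rest. The article gives neither, so both are assumed. (If ages were uniform, 14–15 would be 2 of 12 years, about 17%.) With no true effect of route, the crude contrast is off by f·d.

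Crude rejection is the chance that the 388 versus 388 test is significant in either direction. The last column is the power of a test of under 16 (f·388 people) against everyone else (776 − f·388), with a base rate of 0.5 and pooled variance.

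| f | d | bias f·d | crude rejection | age test alone triggers the model |
|---|---|---|---|---|
| 0.1 | 0.1 | 0.01 | 6% | 22% |
| 0.2 | 0.1 | 0.02 | 9% | 39% |
| 0.3 | 0.1 | 0.03 | 13% | 51% |
| 0.1 | 0.2 | 0.02 | 9% | 70% |
| 0.2 | 0.2 | 0.04 | 20% | 93% |
| 0.3 | 0.2 | 0.06 | 39% | 98% |

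Worked row, f = 0.2 and d = 0.1: 77.6 people at 0.4 against 698.4 at 0.5, pooled rate 0.49. The standard error is 0.0598 under the null and 0.0587 under the alternative. Φ[(0.10 − 1.96·0.0598)/0.0587] = Φ(−0.29) = 0.385.

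With unpooled variance, a base rate of 0.45 and under-16s rating lower, the last column becomes 25% and 42% for d = 0.1 (f = 0.1, 0.2), and 79%, 97% and 99% for d = 0.2 (f = 0.1, 0.2, 0.3).

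**4. The other tests.** Any association triggers the model. If nothing is associated, 8 independent tests (the number of factors in the section 1.2.4 objective) to 11 (the section 2.4.2 sociodemographic list without postal code) still trigger it with probability 1 − 0.95⁸ = 0.34 to 1 − 0.95¹¹ = 0.43.

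Combining the age test with 7 to 10 independent null tests at d = 0.1, the model is not triggered with probability:
- f = 0.1: 0.776·0.95⁷ = 0.54 to 0.776·0.95¹⁰ = 0.46
- f = 0.2: 0.615·0.95⁷ = 0.43 to 0.615·0.95¹⁰ = 0.37

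With a modest age effect, adjustment is close to a coin toss.

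**5. Price of restricting to 16–25.** With 388 own-accord and 388·(1 − f) indicated participants (349, 310 and 272), power for 0.5 versus 0.4 is 0.78, 0.75 and 0.72 at f = 0.1, 0.2 and 0.3.

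**The case against.** The strongest reply is that the condition is loose. Any association, with any sociodemographic variable, brings in the model, and a null result on route itself does not block it. Where age distorts the crude contrast badly, age is strongly related to rating and its test will nearly always be significant: about 93% and 98% at a 20-point gap with a 20–30% share of under-16s. This stands, and it limits the harm.

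A reader might infer several stronger things that the documents do not support:

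- That the main contrasts necessarily stay confounded. They stay crude for certain only if no test is significant.
- That the plan has a 20–39% false-positive rate. Those figures belong to the crude test standing alone, in scenarios where the model would almost always be fitted.
- That sex also differs between routes by design. The documents fix this only for age.
- That p values are distorted by covariate screening. Section 2.6.2 makes the fitting of the model conditional; it states no rule for selecting covariates, and the list may sit in a fuller plan.

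Age is summarised by "mean and standard deviation for age and years living in Spain" yet tested only with categorical methods. That is at most a loss of efficiency and is not relied on here.

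The assumed shares may also be high: universities are included, centres may choose the online form, and double consent hinders recruitment of under-16s. The lower rows of the table allow for this. What remains is that a stated rule lets chance significance decide whether a contrast with a known age imbalance is adjusted.

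**Conclusion.** The point holds in limited form. The condition in section 2.6.2 is a poor rule for a non-randomised comparison, and sections 2.4.2 and 2.5 place all 14–15-year-olds on one side of the contrast that sizes the study. Following the plan as written may leave that contrast confounded by age.

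The exposure is greatest where the age effect is modest. At an assumed 10-point gap and a 10–20% share of under-16s, the age test alone triggers the model about 22–42% of the time, depending on the variance formula and base rate. The bias is then 1–2 points against a planned 10, with crude rejection of about 6–9% against a nominal 5%. At a 20-point gap and a 20–30% share, the crude bias is 4–6 points, but the model would nearly always be fitted.

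Adjustment alone is not a full cure. With nobody under 16 in the own-accord group, a model that includes 14–15-year-olds extrapolates in that age band. All these sizes rest on assumed f and d; the imbalance and the conditional rule are stated in the article.

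**What to change.** Replace the conditional sentence in section 2.6.2 with an unconditional one:

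- Fit the regression with assessment of the website as outcome whatever the bivariate results show. Include recruitment route, age, sex/gender, the Territorial Socio-Economic Index and area of residence. All are already collected. Where results are disaggregated by gender, the gender term drops out of the separate models.
- Keep the bivariate tables as description.
- Restrict the own-accord versus indicated comparison to ages 16–25, the range both groups share. Describe 14–15-year-olds separately, and keep them in the objectives that do not compare routes.
- Do not adjust the route contrast for prior use of the website or prior ASSIR contact. Both are largely determined by route, so adjusting for them could remove the contrast itself.

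The model change costs only wording. The age restriction costs power: 0.80 falls to about 0.78, 0.75 or 0.72 if 10%, 20% or 30% of the indicated group is under 16. The plan should state this figure. Keeping 0.80 would need 388 indicated participants aged 16 or over, which means 388/(1 − f), or 432, 485 or 555 in that group overall.

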#### 2.3.1. Qualitative Part of the Study

The sampling will be theoretical. Participants will have to meet different profiles defined by representativeness criteria specified by the research team in order to provide heterogeneity to the sample and until reaching theoretical saturation of technical data. The representativeness criteria are age (two groups: 14–18 and 19–25), rural and city areas, different socioeconomic conditions, all sexes (male/female/intersex), different gender identities (male, female, transgender, non-binary, fluid and other) and different sexual orientations (heterosexual, homosexual, plurisexual, asexual).

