#### 2.3.2. Quantitative Part of the Study

We have devised three methods for participant recruitment: (1) convenience sampling will be used in education centres (high schools, vocational training schools, training and insertion programs and universities); (2) consecutive sampling will be used to recruit young people who consult the ASSIR units; (3) young people who access the WSJ of their own accord will be invited to participate. These three methods will be used to invite participants to join the study; participation will be voluntary. Recruitment is more fully developed in the data collection Section 2.4.2.

Based on the size of the effect of the differences in the assessment of the WSJ contents, and depending on whether they consulted the website of their own accord or not, a total sample of 776 participants will be required, accepting an alpha risk of 0.05 and a beta risk of 0.2 in a two-sided test. Up to 388 subjects will be necessary in the first group and 388 in the second to find a statistically significant proportion difference, expected to be of 0.5 in group 1 and 0.4 in group 2.

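### The 776 participants give 80% power for one whole-sample comparison only; the plan disaggregates the analysis by gender without saying how the two fit together, and every gender-specific test would have less than 80%

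*Protocol article*

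**What the plan says.** Section 2.3.2 (Sample/Participants, quantitative part) states that "a total sample of 776 participants will be required", "accepting an alpha risk of 0.05 and a beta risk of 0.2 in a two-sided test". It then explains: "Up to 388 subjects will be necessary in the first group and 388 in the second to find a statistically significant proportion difference", with the proportions "expected to be of 0.5 in group 1 and 0.4 in group 2". The two groups are defined by whether the participant came to the website of their own accord. Section 2.4.2, under the variables related to study recruitment, confirms that this variable was the basis of the calculation. No gender mix and no allowance for strata enters it.

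Section 2.6.2 (Data Analysis, quantitative part) plans descriptive summaries, then chi-squared or Fisher tests of assessment against the sociodemographic variables, then a regression if associations appear. Next comes: "The anlaysis will be performed disaggregating by gender. Significance level is set at 5" per cent. The text does not say whether the gender breakdown replaces or supplements a whole-sample analysis, or whether it is inferential or descriptive.

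Section 1.2.4 asks, among its specific objectives, whether assessment of content and usability varies with a list of factors. These include sex, gender identity and the motivation for consulting the website.

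**The concern.** The study is sized as one unstratified comparison, while the analysis is described as carried out by gender. The gender sentence directly follows the tests and the regression and stands beside the significance level, so it is natural to read it as covering the tests as well as the tables. On that reading, each test uses only part of the 388 per group.

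Two things are at stake. First, a real 10-point difference that is the same in every gender would often be missed in one or more of them. Second, a result that is significant in one gender and not in another is a likely chance outcome, and it is easily taken as a gender difference. Separate analyses within gender also cannot answer the question in Section 1.2.4 of whether assessment varies by gender identity, because gender does not vary within a single-gender stratum.

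**Working it through.** **Inputs.** From Section 2.3.2: p1 = 0.5, p2 = 0.4, two-sided alpha 0.05, beta 0.2, 388 per group. The documents give no gender split. The splits below are assumptions: two genders, the same mix in both groups, independent respondents.

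**1. Reproduce the plan's figure.** Pooled-variance formula without continuity correction, with mean proportion 0.45:

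n = [1.960 × √(2 × 0.45 × 0.55) + 0.842 × √(0.5 × 0.5 + 0.4 × 0.6)]² / 0.10²
= [1.960 × 0.7036 + 0.842 × 0.7000]² / 0.01 = 387.3, rounded up to 388.

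This matches exactly. It is the size for a single whole-sample test.

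**2. Power within a gender.** With n per group in the stratum:

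power = Φ[(0.10 × √n − 1.960 × 0.7036) / 0.7000]

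- n = 388 (whole sample): (1.9698 − 1.3790) / 0.7 = 0.844, power 80.1%.
- n = 194 (half): (1.3928 − 1.3790) / 0.7 = 0.020, power 50.8%.

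| Assumed split | n per group, larger / smaller | Power, larger | Power, smaller |
|---|---|---|---|
| 50/50 | 194 / 194 | 50.8% | 50.8% |
| 60/40 | 233 / 155 | 58.3% | 42.5% |
| 75/25 | 291 / 97 | 68.0% | 28.7% |
| 90/10 | 349 / 39 | 75.8% | 14.0% |

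Every entry is below 80%, as it must be for any stratum smaller than the whole. At 194 per group, 0.5 against 0.36 has 79.8% power, so the difference detectable with about 80% power is roughly 14 points rather than 10.

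**3. Discordant results when the true effect is identical in both genders.**

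- 50/50: both significant 0.508² = 26%; exactly one 2 × 0.508 × 0.492 = 50%.
- 75/25: exactly one 0.680 × 0.713 + 0.320 × 0.287 = 58%.

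**4. What a whole-sample test that accounts for gender would give.** For a Mantel-Haenszel test stratified by gender, with a common difference of 0.5 against 0.4, the normal approximation gives about 80% when the gender mix is the same in both groups. It gives 78% when one gender makes up 80% of one group and 60% of the other, and 77% for 90% against 70%.

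**5. Size needed to power each gender separately.** With two equal genders, 4 × 388 = 1552 participants.

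**The case against.** The strongest reply is that some pooled analysis is implied. Section 1.2.4 treats gender identity as a factor, Section 2.4.2 lists it among the sociodemographic variables, and Section 2.6.2 tests assessment against those variables. Gender can be tested as a factor only across genders. Section 2.1.2 also calls the study observational and descriptive, so disaggregation may mean no more than reporting by gender. Subgroup analyses nearly always have less power than the overall one. Finally, no sentence expressly prescribes a test of the sized contrast within each gender, and a condensed article may leave such detail to a fuller document.

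Much of this stands. It rules out three stronger readings that a reader might infer:

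- **That 776 is the wrong number.** It is right for the comparison it names.
- **That 80% power was promised within each gender.** Section 2.3.2 states "a beta risk of 0.2 in a two-sided test" for the two-group comparison only, and a pooled test, if run, keeps that power.
- **That 51% is a ceiling.** It is the value at an equal split; a larger gender has more, up to 76% at 90/10.

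Nor does the list of "different gender identities (male, female, transgender, non-binary, fluid and other" define strata for the questionnaire analysis. It is a sampling criterion of the qualitative part (Section 2.3.1), although gender identity is also a questionnaire variable.

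What the reply does not remove is the unqualified sentence in Section 2.6.2. Nothing in the article marks the disaggregation as supplementary or descriptive, and the sentence stands next to the significance level. This is a statement the article makes and leaves open to a damaging reading, not a detail it merely omits.

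**Conclusion.** The concern holds as a mismatch between the sizing and the stated analysis, not as an error in the sample size. The 80% power belongs to one whole-sample comparison of own accord with professional indication. If Section 2.6.2 is followed literally, power for 0.5 against 0.4 is under 80% in every gender. That conclusion needs no assumed split. The particular figures do: about 51% in each of two equal genders, 68% and 29% at 75/25, and exactly one gender significant in 50% to 58% of studies over that range when the effects are identical. They also assume the same gender mix in both recruitment groups and independent respondents. That discordant results would be misread is a risk, not something the article says will happen. The point deserves correction because gender is central to the aims and the correction is cheap.

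**What to change.** In Section 2.6.2, state that:

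- the comparison of own accord with professional indication is tested once, in the whole sample, with gender as a stratification factor (Mantel-Haenszel) or as a covariate in the regression;
- gender-specific proportions and differences are reported with 95% confidence intervals as descriptive results;
- whether the difference varies by gender is judged by a group-by-gender interaction term, and whether assessment itself varies by gender by the gender term in the whole-sample model, not by setting separate p-values side by side.

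In Section 2.3.2, state that the 80% power applies to the whole-sample comparison only.

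The cost is wording and one extra model term; no more participants are needed. The downside is that gender-specific p-values no longer carry conclusions and the power statement is narrower. The interaction test will itself be imprecise. At an equal split, the standard error of the difference between the two gender-specific differences is √(0.49/194 + 0.49/194) = 0.071, so 80% power needs a gap of about 2.80 × 0.071 = 0.20. A non-significant interaction should therefore not be read as showing that the genders are alike. If separate conclusions within each gender are really intended, the strata must be sized for them, at about 1552 participants for two equal genders.
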